# Optimised treatment of patients with enlarged lateral lymph nodes in rectal cancer: protocol of an international, multicentre, prospective registration study after extensive multidisciplinary training (LaNoReC)

**DOI:** 10.1136/bmjopen-2023-083225

**Published:** 2024-10-16

**Keywords:** Patients, Colorectal surgery, Gastrointestinal tumours, Patient Reported Outcome Measures

## Abstract

**Introduction:**

Inadequate treatment of enlarged lateral lymph nodes (LLNs) in rectal cancer patients is associated with an increased lateral local recurrence (LLR) risk, despite neoadjuvant treatment and total mesorectal excision (TME) surgery. There is a promising role for LLN dissection (LLND) to lower this risk, but this challenging procedure requires appropriate training. This study protocol describes a prospective evaluation of oncological outcomes after standardised treatment based on multidisciplinary training, thereby aiming for a 50% reduction in LLR rate.

**Methods and analysis:**

A prospective registration study will be opened in hospitals in which the involved multidisciplinary team members (radiologists, radiation oncologists, surgeons and pathologists) have received dedicated training to enhance knowledge and awareness of LLNs and in which standardised treatment including LLND has been implemented. Patients with rectal cancer and at least one enlarged LLN (short-axis ≥7.0 mm), or intermediate LLN (short-axis 5.0–6.9 mm) with at least one malignant feature on primary MRI, evaluated by a trained radiologist, are eligible. Patients will undergo neoadjuvant treatment by trained radiation oncologists, followed by TME surgery in combination with a minimally invasive, nerve-sparing LLND performed by trained surgeons. LLND specimens are evaluated by trained pathologists or grossing assistants. The primary outcome is LLR rate 3 years postoperatively. Secondary outcomes are morbidity, disease-free survival, overall survival and quality of life. To demonstrate a significant reduction in LLR rate from 13% (based on historical control data) to 6% after optimised treatment, 200 patients with enlarged LLNs are required.

**Ethics and dissemination:**

The medical ethics board of the Vrije Universiteit Medical Centre (VUMC), the Netherlands, approved the study on 23 November 2022 (reference: 2021.0524). Participating centres must obtain local approval and participants are required to provide written informed consent. Results obtained from this study will be communicated via peer-reviewed medical journals and presentations at conferences.

**Trail registration number:**

NCT04486131, 24 July 2020, https://clinicaltrials.gov/ct2/show/NCT04486131.

STRENGTHS AND LIMITATIONS OF THIS STUDYThe lateral nodal recurrence in rectal cancer (LaNoReC) study is grounded on multidisciplinary training of all specialties involved in the treatment of locally advanced rectal cancer.Monthly meetings for quality control will discuss all new inclusions and surgical lateral lymph node dissection videos, thereby increasing quality and standardisation of eligibility criteria and subsequent treatment.The LaNoReC study will gather data on quality of life and morbidity/functional outcomes, providing novel insights into these aspects of care in Western patients.The non-randomised design is a risk for heterogeneity in treatments but has been chosen due to expected difficult accrual if a specific treatment protocol is imposed and the inability to properly define the control treatment.

## Introduction

 The last few decades have witnessed major improvements in rectal cancer treatment due to the use of MRI for adequate staging, neoadjuvant treatment and the total mesorectal excision (TME) procedure, as reflected by a decrease in the overall local recurrence (LR) rate to 5%–10%.^1^,^3^ Consequently, occurrence of LRs has shifted from a central location to the lateral pelvic compartments, the latter now comprising approximately half of all LRs.^4^ Most likely, these are caused by lymphatic spread to lateral lymph nodes (LLNs) in locally advanced rectal cancer (LARC) in the lower part of the rectum.^4^ When these LLNs are primarily enlarged (short-axis ≥7.0 mm), the percentage of lateral LR (LLR) has been reported to be up to 20% after 5 years following neoadjuvant (chemo)radiotherapy (C)RT and TME.^5^,^7^ LLRs are associated with fewer complete resections, and consequently, poorer survival outcomes compared with recurrences at other sites.^8 9^

Different approaches are used worldwide to treat enlarged LLNs. Eastern surgeons, particularly from Japan, perform an LLN dissection (LLND) to decrease the risk of LLR,^10^ despite the associated morbidity.^11 12^ However, the generalisability of studies supporting LLND’s effectiveness is limited due to exclusions of patients with LLNs ≥10.0 mm and the differences in population and practice between the East and the West.^13^ In the West, physicians primarily rely on neoadjuvant (C)RT to treat enlarged LLNs, or they are erroneously considered as systemic disease, leading to undertreatment resulting in high LLR rates.^11^

With recent publications, awareness concerning the importance of LLNs has gradually increased in the West. The international multicentre study by the Lateral Node Consortium found an increased LLR rate of up to 20% after 5 years for primarily enlarged LLNs (≥7.0 mm), which could be significantly lowered to a 3-year LLR rate of 6% with selective LLND after (C)RT.^6^ A second study, the Snapshot Rectal Cancer 2016 study, included 3057 patients operated on for rectal cancer in 2016 in 67 Dutch centres and demonstrated a 3-year LLR rate of 11% (4 years 15%) for patients with enlarged LLNs after (C)RT+TME.^14^ While some other studies remained inconclusive about the influence of malignant features,^5 15^ that study demonstrated additional prognostic value for the presence of malignant features (round shape, irregular margins, loss of fatty hilum and heterogeneity) in intermediate size LLN (short-axis 5.0–6.9 mm), as presence increases the LLR risk from 2% to 8%.^14 16^ Moreover, in both the Consortium and the Snapshot study, LLN enlargement was not associated with increased distant metastases rates, indicating that enlarged LLNs should be considered a locoregional disease, requiring additional treatment.^11 17^

To further increase awareness and knowledge about lateral nodal disease, the Dutch radiologists, radiation oncologists and surgeons participated in training sessions.^18 19^ Radiologists followed a training session provided by expert radiologists, resulting in better short-axis measurements and anatomical classification of LLNs in cases assessed after the training versus baseline assessment.^20^ Moreover, radiation oncologists participated in several consensus meetings in which delineation variations in a similar case were discussed, leading to a renewed delineation guideline with more specific anatomical landmarks, which guarantees adequate coverage of the lateral compartments. These radiation oncologists also examined the radiotherapy delineations and doses for all LLNs with a short-axisv≥5.0 mm from the Snapshot 2016 study and demonstrated adequate coverage still being associated with considerable LLR risk and that a boost may also not prevent LLR.^21^ This suggests that any additional reduction of LLR rates may only be achieved with LLND surgery.^5 6^

In the Snapshot study, the Dutch surgeons performed node-picking and partial LLNDs, associated with increased LLR rates up to 19%.^22^ Due to a lack of experience, these procedures were sometimes performed together with urologists or gynaecologists.^23 24^ However, both specialties perform such lymphadenectomies for malignancies in the anterior pelvic compartment, and dissect mostly external iliac and the proximal part of the obturator area, while rectal cancer predominantly spreads to the distal part of the obturator and internal iliac compartment. These observations imply that formal LLND, following anatomical borders and resecting both complete obturator and internal iliac compartments, is necessary to successfully decrease the recurrence rates. Since enlarged LLNs are relatively uncommon, this procedure has been centralised in the Netherlands after several consensus meetings organised by the Dutch Society of Colorectal Surgery and 16 surgeons were nominated to follow two hands-on cadaver training sessions to get acquainted with the LLND procedure, with monthly video meetings and proctoring sessions thereafter to ensure further quality improvement.

Due to the retrospective nature of the Consortium and Snapshot studies, neither was able to properly investigate a setting in which all specialties involved are carefully trained and where a standardised formal LLND is performed, after which the uniform clearance of all LLNs within anatomical boundaries can be guaranteed. Therefore, the LaNoReC study is designed to investigate whether adequate recognition and reporting of LLNs by trained radiologists, adequate irradiation by trained radiation oncologists and performing standardised LLND with sufficient training, will successfully decrease LLR rates to below 6% for patients with enlarged LLNs. Moreover, it will evaluate current treatment strategies in patients with intermediate LLNs with malignant features.

### Methods and analysis

### Objectives

The primary objective is to evaluate whether optimisation of multidisciplinary care and nerve-sparing LLND surgery can reduce 3-year LLR rate to below 6% in rectal cancer patients with enlarged LLNs.^6^ The main secondary objectives include distant metastases rate, disease-free survival, overall survival and quality of life after 3 years. Moreover, current treatment strategies for patients with intermediate LLNs with one or more malignant features will be investigated.

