### Statistics

Analyses will be conducted in Statistical Package for the Social Sciences (SPSS, Chicago, Illinois). LR and LLR will be compared with a percentage of 13% obtained from the two historic cohorts (Consortium and Snapshot) using a one-sample z-test. Baseline characteristics will be described using numbers and proportions for categorical variables; for continuous data, means with 95% CIs or medians with IQR will be used according to the distribution of the data. Clinical data will be described including the type of neoadjuvant treatment, resection margin, height of the tumour, tumour stage (cT/cN stage) and threatened mesorectal fascia (≤1 mm distance). For functional outcomes, descriptive statistics will be used, while quality of life will be analysed using repeated measure analyses. To compare subgroups within the LaNoReC study, χ^2^ tests and Fisher’s exact tests will be performed for categorical variables. Differences in continuous variables will be analysed using student’s t-tests or Mann-Whitney U tests, according to the distribution of the data. A p value of ≤0.05 will be considered statistically significant.

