### Sample size

The sample size is based on a historical control group with an average 3-year LLR rate of 13% (11% Snapshot and 16% Consortium) in low LARC with LLNs ≥7.0 mm after (C)RT+TME (without LLND), which is the current standard treatment in Europe.^5 6 14^ It is hypothesised that (C)RT+TME+LLND can reduce this rate to 6%, as found by the Consortium study. A one-group χ^2^ test with a 5% two-sided significance level will have 90% power to detect the difference between the null hypothesis proportion of 0.13 and the alternative proportion of 0.06 when the sample size is 190. If correcting for a drop-out rate of 5%, 200 patients are needed. Included patients in need of more extensive surgery (ie, pelvic exenteration or presumed inability to spare the hypogastric nerves on MRI) will be registered and analysed as a separate cohort since these more extensive tumours have higher LLR rates and cannot undergo nerve-sparing LLND.

Annually, approximately 882 patients present with low LARC and are treated with neoadjuvant therapy in the Netherlands.^14^ Considering 122 (14%) of these patients have LLNs ≥7.0 mm, a minimum 2.5-year inclusion period is needed to achieve the estimated sample size (expecting 60% of eligible patients to be enrolled).^14^ As some of the eligible patients will undergo open surgery, it is expected that the inclusion period may require an extension. An interim analysis will be carried out after the inclusion of the first 75 participants. The goal of this interim analysis is to evaluate early indicators of effectiveness concerning oncological outcomes, particularly LLR rate, and to evaluate safety by examining short-term surgical complications (within 90 days) and early functional outcomes (urogenital dysfunction within 3 months). The results will help improve the preoperative information provided to patients. If the interim analysis reveals a high LLR rate that suggests that the hypothesis may not be achievable or significant morbidity within 3 months of surgery, the study team will consider to prompt the study ahead of time.

Additionally, patients with rectal cancer and an LLN of 5.0–6.9 mm SA with at least one malignant feature will be investigated. For this analysis, a sample size calculation is impossible due to limited data. Therefore, all eligible patients in this group will be collected during the study period.

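### The primary objective names a 3-year LLR rate below 6%, but the planned test and sample size use a null of 13%, so a significant result supports only a rate below 13%

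*Protocol article*

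**What the plan says.** The protocol article uses 6% in two different roles.

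- **As the target.** Under Objectives, the primary aim is to evaluate whether optimised multidisciplinary care with nerve-sparing LLND "can reduce 3-year LLR rate to below 6% in rectal cancer patients with enlarged LLNs". The last paragraph of the Introduction says the study investigates whether this care "will successfully decrease LLR rates to below 6% for patients with enlarged LLNs".
- **As the design alternative.** Under Sample size, "It is hypothesised that (C)RT+TME+LLND can reduce this rate to 6%, as found by the Consortium study". The calculation then contrasts "the null hypothesis proportion of 0.13 and the alternative proportion of 0.06 when the sample size is 190", and the test "with a 5% two-sided significance level will have 90% power to detect the difference". After that, "If correcting for a drop-out rate of 5%, 200 patients are needed".

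Under Statistics, the one inferential comparison for the primary outcome is: "LR and LLR will be compared with a percentage of 13% obtained from the two historic cohorts (Consortium and Snapshot) using a one-sample z-test". The other tests in that section concern subgroups and quality of life; functional outcomes are descriptive. The Abstract and the Discussion describe a reduction from 13% to 6%. No section gives a test, a confidence-limit rule or any other decision rule against 6%.

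**The concern.** A test with a null of 13% answers one question: is the rate different from, and in practice lower than, 13%? The alternative of 6% fixes how many patients are needed if the treatment works as hoped. It is not a threshold that a significant result shows to have been passed. The Objectives section nevertheless words that planning value as the rate to get below.

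The consequence is for the conclusion. This is a single-arm study judged against a historical rate, so much of the claim rests on the pre-stated hypothesis. A significant test reported next to the objective as worded invites the statement that LLR has been brought below 6%, when the data may support only a rate below 13%.

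**Working it through.** **Inputs.** Null 0.13, alternative 0.06, two-sided 5%, power 90%, 190 evaluable patients, 5% drop-out (all from Sample size); one-sample z-test against 13% (Statistics); target below 6% (Objectives, Introduction).

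**1. The plan's own sample size.** With the normal approximation for one proportion,

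n = [z(0.975)·√(p0(1−p0)) + z(0.90)·√(p1(1−p1))]² / (p0−p1)²

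= [1.960·√(0.13·0.87) + 1.282·√(0.06·0.94)]² / 0.07² = 189.45, rounded up to 190.

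Drop-out: 190/0.95 = 200. Both stated figures reproduce. The approximate power at 190 is 90.1%.

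**2. Where the test becomes significant.** Critical proportion = 0.13 − 1.96·√(0.13·0.87/190) = 0.0822, and 190·0.0822 = 15.6, so the test is significant at 15 or fewer LLRs. Check: 15 events give z = −2.09 and 16 events give z = −1.88.

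- 15/190 = 7.9%, Wilson 95% CI 4.8% to 12.6%.
- 12 to 15 events (6.3% to 7.9%) reject 13% although the estimate itself is above 6%.

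**3. Chance of a significant result, by true rate.** P(X ≤ 15) for X ~ Binomial(190, p):

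| True 3-year LLR | P(significant against 13%) | Is the rate below 6%? |
|---|---|---|
| 5% | 0.97 | yes |
| 6% | 0.89 | no (equal) |
| 7% | 0.74 | no |
| 8% | 0.55 | no |
| 9% | 0.35 | no |

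**4. What an estimate under 6% would show.** The largest count with an estimate below 6% is 11 (0.06·190 = 11.4). 11/190 = 5.8%, Wilson 95% CI 3.3% to 10.1%. The interval includes 6%.

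**5. What it would take to show a rate below 6%.** Take this to mean an upper 95% limit below 6%. The Wilson upper limit is 5.3% at 4 events and 6.01% at 5 events, so 4 or fewer LLRs (2.1%) are needed. The protocol states no true rate below 6%, so the rates here are assumptions. The second column is P(X ≤ 4) with n = 190. The third uses the formula in step 1 with p0 = 0.06.

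| Assumed true rate | Power with 190 | Evaluable n for 90% power |
|---|---|---|
| 5% | 3.7% | 5547 |
| 4% | 12.0% | 1284 |
| 3% | 32.3% | 520 |
| 2% | 66.8% | 260 |

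**The case against.** The strongest reply is that nothing operative is in doubt. Statistics names the test and the reference value, Sample size names null and alternative, and the Abstract and the Discussion also take 13% as the starting point. The objective says that the study will evaluate whether the rate can be reduced, not that it will show it, and a registration study can meet an evaluative aim by estimation. The target below 6% stands in two sentences only.

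Most of this is right, and it limits the point. Three stronger conclusions might be inferred, and the document does not support them:

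- **That the success criterion is undefined and could be chosen after the fact.** The test against 13% is explicit. What remains is a risk that its result is described against the wrong value.
- **That the study lacks power because, at a true rate of 6%, it has only a 1% chance of an upper limit below 6%.** At a true rate of exactly 6% the statement that the rate is below 6% is false. That 1% is a false-positive probability, which ought to be low. Power has to be judged at true rates below 6%, as in step 5.
- **That about 36% of such studies would be significant yet miss the objective.** At a true 6% the chance of significance is 0.89 and of an estimate below 6% is 0.53, a difference of 0.36. This treats the objective as a rule on the point estimate, which the protocol does not set, and it cannot be combined with figures based on an upper limit.

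The evaluative wording does not remove the mismatch. The question put is still about 6%, and the one planned test answers a question about 13%. A statistical analysis plan, not shown here, could add detail, but the discrepancy lies between sections of the same article.

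**Conclusion.** The point stands as a mismatch between the stated objective and the tested hypothesis. It is not an error in the sample size or the test: 190 and 200 are correct for 13% against 6%.

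An observed rate as high as 7.9% would be significant, and a true rate of 7% or 8% would give significance in about three quarters or just over half of such studies. An upper 95% limit below 6% is out of reach at plausible rates: power is about 4%, 12% and 32% at assumed true rates of 5%, 4% and 3%.

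The figures assume 190 evaluable patients and a binomial count of LLRs at 3 years. The powers against 6% also rest on assumed rates and on reading the target as a rule on the upper limit. The logical point, that rejecting 13% supports only a rate below 13%, needs none of these assumptions. This should be fixed, but it does not invalidate the primary analysis.

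**What to change.** Reword the primary objective under Objectives, and the matching sentence in the Introduction, along these lines: to evaluate whether the 3-year LLR rate in patients with enlarged LLNs is lower than the historical 13%, with 6% as the anticipated rate used for sizing. State that the estimate will be reported with its 95% CI, and that a significant test against 13% will not be presented as showing a rate below 6%. No second test or decision rule against 6% is needed.

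The test, the sample size and the data collection stay as they are. The cost is two edited sentences, one added statement and a less ambitious headline claim. Keeping a rate below 6% as the claim to be tested would instead need a null of 6%, an assumed true rate below it, and 260 (true rate 2%) to 5547 (true rate 5%) evaluable patients for 90% power.

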### Study design

The LaNoReC study is an international multicentre prospective registration study endorsed by the Dutch Colorectal Cancer Group. This study started in 2021 but was temporarily paused due to a major protocol revision. The initial protocol imposed a specific treatment (C(RT) without a boost, restaging MRI and LLND), which would have a major impact on accrual. Therefore, the protocol evolved towards the current prospective registration study, as demonstrated in figure 1. Approximately 38 Dutch hospitals, in which the multidisciplinary team has sufficed the training demands, will be open to include patients. International centres can join after following similar training sessions as the Dutch clinicians, which are organised by the LaNoReC study team. All included patients will undergo optimised standard of care, including MRI assessment by a trained radiologist, neoadjuvant radiotherapy delineation by a trained radiation oncologist, nerve-sparing LLND by a trained surgeon and evaluation of the resection specimen by a trained pathologist or grossing assistant. The study is registered at clinicaltrial.gov: NCT04486131.

**Figure 1 F1:**
[figure not shown]
Flowchart outline of study. CASTOR, an electronic system to safely collect medical data in case report forms; LLN, lateral lymph node; LLND, lateral lymph node dissection; SA, short-axis.

### Study population

Eligible patients have a biopsy-proven adenocarcinoma of the rectum and at least one enlarged LLN of ≥7.0 mm (SA) irrespective of other features, located in a lateral compartment (internal iliac or obturator) or at least one intermediate LLN of 5.0–6.9 mm (SA) in combination with one or more malignant features (round shape, irregular margins, loss of fatty hilum or heterogeneity) on primary MRI.

Patients are not eligible if they are younger than 18 years old, have undergone previous pelvic radiotherapy, have previously undergone an LLND for a pelvic malignancy, have synchronous distant metastases, have synchronous stage III/IV colon cancer, have had another malignancy in the previous 3 years which could affect oncological outcomes (these patients must first be discussed with the research team to determine inclusion or exclusion), have an absolute contraindication for general anaesthesia, have familial adenomatous polyposis or are pregnant.

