### Nerve-sparing LLND procedure by trained surgeons

LLNDs will only be performed by a select team of surgeons after completing adequate human cadaver training, intensive proctoring and assessment of procedural videos. Only surgeons who participated in this training can be nominated with their hospital to act as referral centre or the surgeons can be invited to perform the resection in the (local) referring centre. All ‘study-LLND’ procedure videos will be discussed during monthly meetings for quality control.

Patients with primarily enlarged (≥7.0 mm SA) LLNs are advised to undergo an LLND. Moreover, LLND should be considered in patients with an intermediate (5.0–6.9 mm SA) LLN with at least one malignant feature. LLNDs should be performed according to a minimally-invasive, nerve-sparing technique. If preoperative MRI shows the lateral extension of the tumour into the nerve plexus or an exenteration is required, the patient will still be included to analyse oncological and functional outcomes; however, the patient is not included in the main analyses (see sample size section). If in a shared decision-making process, the patients decide not to undergo an LLND, they remain in the study and are followed for collection of oncological outcomes. In case of a complete clinical response of the tumour and shrinkage of the LLN(s), a patient may enter a watch-and-wait protocol; in these cases, patients should be closely monitored and an LLND may be omitted.

The surgical technique for LLNS has been previously described in detail.^24^ The procedure involves the excision of all lateral lymphatic tissues within the internal iliac and obturator compartment along three anatomical planes: (1) the medial plane defined by the ureter and pelvic plexus (ureterohypogastric fascia), (2) the lateral plane bounded by the psoas and internal obturator muscle and (3) the dorsal plane defined by the internal iliac vessels and the sciatic nerve. It is important to note that the lymphatic tissue along the external iliac arteria is not dissected during this procedure.

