The inclusion criteria for the LaNoReC study are based on the Snapshot and the Consortium study, in which the combination of (C)RT and TME was insufficient for adequate treatment of patients with enlarged LLNs.^5 14^ Besides short-axis size, the recurrence rates seem to be also influenced by other radiological criteria, such as the presence of malignant features which increased the LLR rate in intermediate LLNs to 8% (vs 2% in absence of malignant features). In enlarged nodes, the presence of two or more malignant features was associated with an increased LLR rate of 17% after 4 years, while no LLR developed if such features were absent. Since the influence of malignant features has only been described in small subgroups and should be interpreted with caution, the inclusion criteria and LLND recommendations for the LaNoReC study are based on short-axis size only for enlarged nodes and intermediate nodes specifically combined with the presence of malignant features. By including this intermediate node group, the LaNoReC study aims to dissolve the current lack of knowledge regarding treatment options and oncological outcomes in those patients. After thorough evaluation during multidisciplinary meetings and a shared decision-making process with the patient, an LLND can be considered to lower the LLR rate.

The inclusion criteria described in the previous paragraph should be based on primary MRI, as the Consortium study is the only study which found that sufficient downstaging on restaging MRI (shrinkage of iliac and obturator LLNs to ≤4 mm and ≤6 mm, respectively) could avoid LLND.^5^ The Snapshot study, however, showed that downsizing of LLNs below the Consortium cut-offs still resulted in an unacceptably high LLR rate of up to 15%.^14^ The inclusion criteria for the LaNoReC study are based on the results of the Snapshot study because of the high validity of these findings due to the training of radiologists. Exempted from this are those with a complete clinical response for which a watch-and-wait trajectory is increasingly applied. Although these patients were not included in the Snapshot study, and therefore restaging results are not applicable to this group, we believe an LLND can be omitted in these cases and close surveillance is justified.

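### The fixed 13% benchmark describes low locally advanced rectal cancer treated with TME, but the eligible and analysed population is drawn differently, and the single-arm test is sensitive to such a shift

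*Protocol article*

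**What the plan says.** **Benchmark.** The Sample size section names its comparator: "historical control group with an average 3-year LLR rate of 13% (11% Snapshot and 16% Consortium) in low LARC with LLNs ≥7.0 mm". Those patients had (C)RT+TME and no LLND. Accrual is also projected from low LARC treated with neoadjuvant therapy. The Statistics section compares LLR with this 13% by a one-sample z-test and states no case-mix adjustment.

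**Eligibility.** The Study population section reads "Eligible patients have a biopsy-proven adenocarcinoma of the rectum and at least one enlarged LLN" of at least 7.0 mm, or an intermediate node with a malignant feature. Neither the inclusion nor the exclusion criteria mention tumour height or local stage.

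**Removal after inclusion.** Patients needing exenteration, or whose hypogastric nerves are presumed on MRI not to be spareable, "will be registered and analysed as a separate cohort since these more extensive tumours have higher LLR rates". The surgical section confirms that they are not in the main analyses.

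**Watch-and-wait.** After a complete clinical response with nodal shrinkage, "a patient may enter a watch-and-wait protocol" and LLND may be omitted. The Discussion says of them: "Although these patients were not included in the Snapshot study, and therefore restaging results are not applicable to this group". No text removes them from the main analysis and none places them in it. The Abstract times the primary outcome at 3 years after surgery.

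**The concern.** With no concurrent control, the 13% is the whole control arm. It has to be the rate that the analysed patients would have had without the optimised treatment. The text departs from that in three places.

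1. Benchmark and accrual are restricted to low LARC, and eligibility is not. The Introduction links lateral recurrence mainly to LARC of the lower rectum, so patients outside that group may carry a lower risk.
2. A group is taken out of the trial side because its prognosis is worse, and nothing says whether the historical rate was restricted in the same way. The surgical section refers to preoperative MRI for nerve-plexus extension and to exenteration being required, so the classification is not tied to the primary MRI and could follow the response to neoadjuvant treatment.
3. Watch-and-wait patients have no time origin for the endpoint and no stated place in the analysis.

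If the analysed patients would have had fewer than 13% LLRs anyway, the trial can reject 13% through case mix alone.

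**Working it through.** **Inputs from the Sample size section.** Null 0.13, alternative 0.06, n=190, two-sided 5%, 90% power, 5% drop-out.

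**Reproducing the plan's figure.** n = [(1.960·√(0.13·0.87) + 1.2816·√(0.06·0.94)) / (0.13 − 0.06)]² = [(1.960·0.3363 + 1.2816·0.2375) / 0.07]² = 189.45, so 190; 190/0.95 = 200. The arithmetic is sound. The question is comparability.

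**Rejection region.** The standard error under the null is √(0.13·0.87/190) = 0.0244. With 15 LLRs (7.9%), z = (0.0789 − 0.13)/0.0244 = −2.09; with 16 (8.4%), z = −1.88. Success therefore needs at most 15 LLRs in 190.

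**Chance of success with no treatment effect**, exact binomial P(X ≤ 15 | 190, p):

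| Underlying rate p | Chance of success |
|---|---|
| 14% | 0.7% |
| 13% (as planned) | 1.9% |
| 12% | 4.6% |
| 11% | 10.1% |
| 10% | 20.1% |

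For scale, the two source cohorts have rates of 11% and 16%, so a two-point shift is no larger than the gap between the pooled figure and one of its components.

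**What could produce such a shift.** The documents give none of the shares or subgroup rates below; they are assumptions.

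- 10% of patients outside low LARC with 5% LLR: 0.9·0.13 + 0.1·0.05 = 12.2%, chance of success 3.9%.
- 20% of patients outside low LARC with 5% LLR: 0.8·0.13 + 0.2·0.05 = 11.4%, chance 7.5%.
- Removing a 10% subgroup with 30% LLR, if the 13% contains such patients: (0.13 − 0.10·0.30)/0.90 = 11.1%, chance 9.3%.

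**The opposite direction.** If the treatment achieves 6% but 20% of patients decline LLND and stay at 13%, the overall rate is 0.8·0.06 + 0.2·0.13 = 7.4%, and exact power falls from 89% to 67%.

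**The case against.** A reader might infer that every mismatch favours success, and might stack them: 20% outside low LARC at 5% LLR, removal of 10% exenteration cases at 25%, and 10% watch-and-wait at 3%. The removal leaves (0.13 − 0.10·0.25)/0.90 = 11.67%. The mix is then 0.7·0.1167 + 0.2·0.05 + 0.1·0.03 = 9.5%, with a false-success chance of about 28%. The documents do not support this. All three shares and all three rates are invented, and all point one way.

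Several features weaken that reading:

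- The benchmark is a TME cohort, and the protocol treats exenteration as more extensive surgery. The 13% may already omit those cases, in which case separating them improves the match.
- Watch-and-wait patients are in the main analysis only by silence. A patient without surgery cannot contribute to a postoperative endpoint as worded, and the tested hypothesis concerns (C)RT+TME+LLND.
- RAPIDO patients are included despite a reported higher local recurrence rate, and an advised 24-month MRI may detect more recurrences than retrospective cohorts did. Both could raise the observed rate. Patients who decline LLND stay in the study, which costs power.
- Every patient has a qualifying node and neoadjuvant treatment containing radiotherapy, so few early tumours may enter.
- An analysis plan that is not shown may define the analysis sets.

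These points stand against any claim about net direction or size. They do not restore comparability. Eligibility, benchmark and the prognosis-based removal are all stated in the protocol and differ from one another, and opposing mismatches of unknown size still leave 13% without a matching population.

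**Conclusion.** The concern holds as a mismatch between the population that produced the 13% and the population to be compared with it. It does not hold as a demonstrated bias towards success. The firm part is textual: low LARC in the benchmark against no height or stage limit in eligibility; removal for worse prognosis with no stated counterpart in the historical rate; and watch-and-wait patients with neither a time origin nor an assigned place. The size is conditional. A no-effect rate one to three points below 13% would raise the chance of false success from 1.9% to between 4.6% and 20.1%, while one point above would lower it to 0.7%. These figures assume n=190, a binary 3-year outcome and the fixed 13% null. Which row of the table applies cannot be determined from the documents. This should be fixed, because the primary conclusion rests on this one comparison.

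**What to change.** These changes concern analysis sets only and alter no treatment.

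1. Define the primary analysis set to match the benchmark: a node of at least 7.0 mm, low LARC, TME performed, time counted from surgery. Tumour height and cT/cN stage are already to be described.
2. Analyse other tumour heights and stages, and watch-and-wait patients, as separate cohorts, with watch-and-wait timed from the end of neoadjuvant treatment.
3. For analysis, assign exenteration and plexus status from the primary MRI, so that response to treatment cannot move a patient between cohorts.
4. Report sensitivity analyses of all patients with nodes of at least 7.0 mm including the exenteration cohort, and with and without watch-and-wait.
5. Where the historical data are accessible, recompute the benchmark with the same restrictions.

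**Cost.** Mostly wording and tabulation. Some enrolled patients move to secondary sets, so the primary set may fill more slowly, although accrual was already projected from low LARC. Step 5 depends on data access and could expose a power problem. By the same sample-size formula, a matched benchmark of 12%, 11% or 10% against 6% would need 247, 337 or 498 patients for 90% power, and 190 patients would give about 79%, 63% or 44%.
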